## Protocol Summary

### Title

**A randomized, open label, phase II study: stereotactic body radiotherapy vs. conventional intensity-modulated radiotherapy for low- or intermediate-risk prostate cancer in an Asian population**

### Objectives

#### Primary Objective

- To compare the 1-year health-related quality of life (HRQOL) between SBRT and IMRT as measured by the Bowel and Urinary domains of the Expanded Prostate Cancer Index Composite (EPIC) instrument.

#### Secondary Objectives

- To estimate the rate of acute and late GI and GU toxicity for each arm at 1, 2, and 5 years
- To estimate biochemical-failure free survival in each arm at 1, 2, and 5 years
- To estimate disease-specific survival in each arm at 1, 2, and 5 years
- To estimate overall survival in each arm at 1, 2, and 5 years

### Design

|                 |                                                   |                  |                                                                                               |
|-----------------|---------------------------------------------------|------------------|-----------------------------------------------------------------------------------------------|
| Stratify | Risk group
1. Low risk
2. Intermediate risk | Randomize | Arm 1
Conventional IMRT
76Gy in 38 fractions of 2 Gy over 7.5 weeks       |
|                 |                                                   |                  | Arm 2
SBRT
36.25Gy in 5 fractions of 7.25Gy, twice a week over 15-17 days |

### Patient population

Patients with low or intermediate risk ( i.e. T1-T2c and PSA < 20 and Gleason score <8) clinically localized prostate cancer

## Title

**A randomized, open label, phase II study: stereotactic body radiotherapy vs. conventional intensity-modulated radiotherapy for low- or intermediate-risk prostate cancer in an Asian population**

### 1.0 Introduction

Radiotherapy is a common treatment alternative for prostate cancer and patients are commonly treated daily over a period from 7-8 weeks. Recent analysis of the tumour biology of prostate cancer has suggested that it is more sensitive to larger dose per fraction (1-5). Appropriately designed schedules using large fractions (i.e. hypofractionated regimen) could result in increases in biochemical control with no increase in late sequelae. In addition to the potential for significant therapeutic gain, if a hypofractionated regimen is found to produce comparable findings it would result in substantial health care cost savings and would also be more convenient for patients.

Results of those hypofractionated randomized trial came from Canada and has been published (8). The trial compared 66 Gy/33 fractions (Long arm) to 52.5 Gy/20 fractions (Short arm) in men with low- and intermediate-risk prostate cancer. In this trial the 5-year rate of failure (biochemical or clinical) was higher in the Short arm compared to the Long arm (59.95% vs. 52.95%; HR 1.18 [0.99-1.41],  $p < 0.05$ ). At first glance this would appear to suggest that the hypofractionated regimen may be inferior compared to a conventionally fractionated regimen, but the two arms were not designed to be isoeffective. In fact, using the biologically effective dose, the Short arm is consistently less than the Long arm until the alpha-beta ratio reaches a value of  $< 1$ . The results of the Canadian trial, therefore, are not inconsistent with an alpha-beta ratio for prostate cancer of 1.5. At a median follow-up of 5.7 years there was no difference in 5-year actuarial rate of late grade 3+ GI/GU toxicity between the two arms.

In recent years investigators have looked at even shorter radiotherapy schedules (i.e. Stereotactic body radiotherapy (SBRT)). Stanford reported on 41 low risk patients treated with 36.25 Gy in 5 fractions using stereotactic body radiotherapy (6-7). The first 21 patients were treated on consecutive days but, due to higher than expected rectal toxicity treatments were modified to be given every other day (three fractions a week). With these changes no patients experienced Grade 3 or higher toxicity.

The below table summarizes the published SBRT studies (6-7, 9-12), all of which are single-arm phase I/II trials, and most of which involve  $< 100$  patients. Toxicity appears acceptable, having consisted primarily of grade 2 complications and grade 3 complications are rare. The biochemical control looks promising in these studies.

| Author | Sample size | Median follow-up (Months) | Regimen | Grade 2 or above toxicity | Freedom from biochemical |
|--------|-------------|---------------------------|---------|---------------------------|--------------------------|
|--------|-------------|---------------------------|---------|---------------------------|--------------------------|

|           |     |      |                | (%)               | failure (%) |
|-----------|-----|------|----------------|-------------------|-------------|
| Madsen    | 40  | 41   | 33.5Gy/6.7Gy   | GU: 20
GI: 7.5 | 90          |
| King      | 67  | 32   | 36.25Gy/7.25Gy | GU: 8.5
GI: 2  | 94          |
| Friedland | 112 | 24   | 35Gy/7Gy       | <10               | >95         |
| Katz      | 304 | 30   | 36.25Gy/7.25Gy | <10               | >95         |
| Mcbride   | 45  | 44.5 | 37.5Gy/7.5Gy   | GU: 19
GI: 12  | 98          |
| Boike     | 45  | 30   | 45Gy/9Gy       | GI: 18
GU: 31  | 100         |

The efficacy and tolerability of SBRT for the Chinese prostate cancer patients remains unresolved. As the incidence of prostate cancer is mounting, it is beneficial, from the cost-effectiveness point-of-view, to investigate the feasibility of shorter radiotherapy regimen in Chinese prostate cancer patients, in which more patients can be treated within the same period of time and the travelling time to radiotherapy centre (from 7-8 weeks to 2 weeks) would be largely reduced.

## **2.0 Objectives**

### **Primary Objective**

- To compare the 1-year health-related quality of life (HRQOL) between SBRT and IMRT as measured by the Bowel and Urinary domains of the Expanded Prostate Cancer Index Composite (EPIC) instrument.

### **Secondary Objectives**

- To estimate the rate of acute and late GI and GU toxicity for each arm at 1, 2, and 5 years
- To estimate biochemical-failure free survival in each arm at 1, 2, and 5 years
- To estimate disease-specific survival in each arm at 1, 2, and 5 years
- To estimate overall survival in each arm at 1, 2, and 5 years

## **3.0 Patient Selection**

Patients from the both the Department of Clinical Oncology and Surgery are potential candidates to be recruited into this study.

### **Conditions for Patient Eligibility**

- Histological confirmation of prostate adenocarcinoma
- Low or intermediate risk prostate cancer patients (i.e. T1-T2c and PSA < 20 and Gleason score < 8) with the risk of pelvic node metastasis  $\leq 15\%$  as calculated by Roach's formula
- ECOG performance score 0-1
- Age  $\geq 18$
- History/physical examination within 2 weeks prior to registration
- Able to sign informed-consent

#### Conditions for Patient Ineligibility

- Patients with previous diagnosis of cancer other than prostate cancer and non-melanoma skin cancer.
- Evidence of distant metastases
- Regional lymph node involvement
- Previous radical surgery (prostatectomy), cryosurgery, or HIFU for prostate cancer
- Previous pelvic irradiation, prostate brachytherapy, or bilateral orchiectomy
- Previous hormonal therapy, such as LHRH agonists (e.g., goserelin, leuprolide) or LHRH antagonists (e.g., degarelix), anti-androgens (e.g., flutamide, bicalutamide), estrogens (e.g. DES), or surgical castration (orchiectomy)
- Unstable angina and/or congestive heart failure requiring hospitalization, transmural myocardial infarction within the last 6 months, acute bacterial or fungal infection requiring intravenous antibiotics, chronic obstructive pulmonary disease exacerbation or other respiratory illness requiring hospitalization or precluding study therapy at the time of registration
- Patients who have received prior chemotherapy.

#### **4.0 Pre-treatment evaluation and management**

Patients recruited into this study are required to complete the investigation including MRI pelvis. Bone scan will be required if clinically suspicious of bone metastasis. Besides, three gold fiducial markers will be inserted into the prostate under trans-rectal ultrasound (TRUS). The markers will be inserted in different planes within the prostate in order to facilitate the visualization of these markers in the on-board imaging at antero-posterior and lateral position.

#### **5.0 Radiotherapy**

##### **1. Treatment planning and delivery**

###### **A. Patient set-up**

- Patients will be positioned supine in a comfortable posture with Vaclock. Patients will be asked to drink 400cc water 1 hour before the simulation and each treatment. Patients will be asked to empty the rectum before the simulation and each treatment. Dulcolax will be given and will be used when necessary for the purpose of emptying the rectum. Patients will be advised to adhere to a low gas, low motility diet commencing one day prior to the treatment. The use of rectal balloons will be allowed but not mandatory.

###### **B. Simulation/planning CT**

- CT will be the primary image platform for treatment planning. The simulation should be performed in the supine treatment position, with the fiducial markers/rectal balloon in place (where utilized). Axial cuts of 3 mm or less will be acquired throughout the pelvis and prostate from the top of the iliac crests superiorly to the perineum inferiorly.

###### **C. Target volumes**

###### **Arm 1**

- The clinical target volume (CTV1) will be the whole prostate as defined by the non-contrast axial planning CT scan for the low risk group of patients. For intermediate risk group of patients, apart from CTV1, another clinical target volume(CTV2) will be

the whole prostate plus proximal two-third of seminal vesicles. MRI will be co-registered with the planning CT scan to aid for target contouring. The planning target volume (PTV) will be defined as the CTV plus 10 mm margin posteriorly and 6 mm in all other direction. To meet dose constraints, if necessary, the anterior margin can be reduced to 5mm.

#### Arm 2

- The clinical target volume (CTV1) will be the whole prostate as defined by the non-contrast axial planning CT scan for the low risk group of patients. For intermediate risk group of patients, apart from CTV1, another clinical target volume (CTV2) will be the whole prostate plus proximal two-third of seminal vesicles. MRI will be co-registered with the planning CT scan to aid for target contouring. The planning target volume (PTV) will be defined as the CTV plus 3 mm margin posteriorly and 5 mm in all other direction. To meet dose constraints, if necessary, the anterior margin can be reduced to 3 mm.

#### D. Critical structures

- The normal tissue volume to be contoured will include bladder, rectum, bilateral femora (to the level of ischial tuberosity) and penile bulb. The bladder should be contoured from its base to the dome. The rectum should be contoured from the anus (at the level of the ischial tuberosities) for a length of 15 cm or to the rectosigmoid flexure. This generally is below the bottom of the sacroiliac joints.

#### E. Dosimetry

- Total prescribed dose

#### Arm 1

- Patients will receive 38 fractions of radiation, each fraction size will be 2Gy. The total dose will be 78Gy to PTV 1. Whereas the total dose will be 70Gy over 38 fractions to PTV 2. The treatment will be delivered 5 fractions per week consecutively except public holiday, and the total duration of treatment will be 7.5 to 8 weeks.

#### Arm 2

- Patients will receive 5 fractions of radiation; each fraction size will be 7.25Gy. The total dose will be 36.25 Gy to PTV1. Whereas the total dose will be 32.5Gy over 5 fractions to PTV2. The 5 treatments will be scheduled to be delivered twice a week over approximately 15-17 days. A minimum of 72 hours and a maximum of 96 hours should separate each treatment. No more than 2 fractions will be delivered per week. The total duration of treatment will be no shorter than 15 days and no longer than 17 days.
- Dose coverage
  - The isodose line used for the prescription dose should cover a minimum of 95% of the PTV.
- Minimum dose
  - The minimum dose within the PTV to a point that is 0.03 cc in size must be  $\geq 95\%$  of the prescribed dose.
- Planning technique
  - RapidArc plans were generated using double arcs, operating two complementary coplanar arcs of 350° (one counter-clockwise from 175° to

185°, one clockwise from 185° to 175°). Two arcs were used in order to achieve dose distributions with higher dose homogeneity in the targets, and lower maximum and mean doses to the OARs. The field size was set manually to include the whole tumor 3-dimensionally and the collimator was twisted 20 degrees to reduce the tongue-and-groove effect to the organs next to the target. Dose intensity modulation was achieved by the continuous variation of the gantry speed, dose rate and MLC positions. RA plan optimization was based on the Progressive Resolution Optimization (PRO) algorithm using five levels of optimization at a total of 177 checkpoints.

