#### F. Dose constraint/specification

##### Arm 1

| PTV                          | Dmin ≥ 95% of prescribed dose
≤3% received >107% of prescribed dose
≤3% received <93% of prescribed dose |
|------------------------------|----------------------------------------------------------------------------------------------------------------|
| rectum                       | V75Gy ≤ 15%
V70Gy ≤ 20%
V65Gy ≤ 25%
V60Gy ≤ 35%
V50Gy ≤ 50%                                        |
| bladder                      | V80Gy ≤ 15%
V75Gy ≤ 25%
V70Gy ≤ 35%
V65Gy ≤ 50%                                                       |
| femoral head                 | V50Gy ≤ 50%                                                                                                    |
| penile bulb
(recommended) | D70 ≤ 70Gy
D90 ≤ 50Gy                                                                                       |
| normal tissue                | Dmax ≤ 110% of prescribed dose                                                                                 |

##### Arm 2

| Organ           | Volume                              | Dosimetry parameters |
|-----------------|-------------------------------------|----------------------|
| Prostate (PTV1) | Maximum point dose (1 cc)           | ≤38.78Gy             |
|                 | Minimum dose received by 95% of PTV | ≥ 36.25 Gy           |
|                 | Minimum dose received by PTV        | ≥ 34.4 Gy            |
| Prostate (PTV2) | Maximum point dose (1 cc)           | ≤38.78Gy             |
|                 | Minimum dose received by 95% of PTV | ≥ 32.5Gy             |
|                 | Minimum dose received by PTV        | ≥ 30.9Gy             |
| Rectum          | Maximum point dose (1 cc)           | ≤ 38.06 Gy           |
|                 | Less than 3 cc                      | < 34.4 Gy            |
|                 | 90% rectum                          | ≤ 32.625 Gy          |
|                 | 80% rectum                          | ≤29 Gy               |

|                                     |                                         |                                        |
|-------------------------------------|-----------------------------------------|----------------------------------------|
|                                     | 50% rectum                              | $\leq 18.125$ Gy                       |

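### The Arm 1 (IMRT) prescription contradicts itself: 38 fractions of 2 Gy make 76 Gy, as in the design table, but the dosimetry section gives a total of 78 Gy to PTV1

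*Protocol*

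**What the plan says.** The Arm 1 prescription appears in two places in the protocol.

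- **Protocol Summary, Design table:** "76Gy in 38 fractions of 2 Gy over 7.5 weeks".
- **Section 5.0 E, Dosimetry, Arm 1:** "Patients will receive 38 fractions of radiation, each fraction size will be 2Gy. The total dose will be 78Gy to PTV 1". For the second target volume it adds: "Whereas the total dose will be 70Gy over 38 fractions to PTV 2".

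Section 5.0 F then sets Arm 1 planning limits relative to the prescription. For the PTV the minimum is "Dmin ≥ 95% of prescribed dose", with further limits at 107% and 93%. For normal tissue it is "Dmax ≤ 110% of prescribed dose". That table does not say how many Gy the prescribed dose is. The Arm 1 rectum, bladder, femoral head and penile bulb limits in the same table are in absolute Gy.

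**The concern.** Fraction number, fraction size and total dose are tied by a simple product, so any two fix the third. The dosimetry section states all three for Arm 1 PTV1, and they do not fit together. The total also differs from the design table, although fraction number and fraction size are the same in both places.

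This is the operative prescribing text for the control arm. Two planners could work to different totals, each citing the protocol, which makes it a patient-safety matter first. It also bears on interpretation. Section 8.0 tests each arm separately on 1-year EPIC bowel and urinary decline, so the IMRT verdict would attach to a dose that the protocol does not pin down. The primary objective compares SBRT with IMRT, and that comparison would have an uncertain reference. With about 30 eligible patients per arm, any mixture of prescriptions could not be reliably separated afterwards.

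**Working it through.** **Inputs.** Arm 1: 38 fractions, 2 Gy each (Design table and 5.0 E); total 76 Gy (Design table) or 78 Gy (5.0 E); PTV2 70 Gy over 38 fractions (5.0 E). Arm 2: "Patients will receive 5 fractions of radiation; each fraction size will be 7.25Gy", total 36.25 Gy (Design table and 5.0 E).

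**1. Can the stated totals be reproduced?** Total = fractions × dose per fraction.

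- Arm 2: 5 × 7.25 = 36.25 Gy. Reproduced exactly.
- Arm 1, Design table: 38 × 2 = 76 Gy. Reproduced.
- Arm 1, Dosimetry section: 38 × 2 = 76 Gy, against 78 Gy stated. Not reproduced; the gap is 2 Gy, and 2/76 = 2.6%.

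**2. What would 78 Gy require?**

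- At 2 Gy per fraction: 78/2 = 39 fractions.
- In 38 fractions: 78/38 = 2.053 Gy per fraction.

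The protocol states neither.

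**3. Does other text settle it?**

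- *PTV2:* 70/38 = 1.842 Gy per fraction. This is a separate, lower dose level and does not account for the 2 Gy.
- *Treatment time:* at 5 fractions a week, 38/5 = 7.6 weeks and 39/5 = 7.8 weeks. Both lie within the 7.5 to 8 weeks given in 5.0 E.
- *Planning limits:* the Arm 1 percentages move with the total.

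| Arm 1 limit (5.0 F) | If 76 Gy | If 78 Gy |
|---|---|---|
| PTV minimum, 95% | 72.2 Gy | 74.1 Gy |
| PTV low threshold, 93% | 70.7 Gy | 72.5 Gy |
| PTV high threshold, 107% | 81.3 Gy | 83.5 Gy |
| Normal tissue maximum, 110% | 83.6 Gy | 85.8 Gy |

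In Arm 2 the corresponding target limits are given in Gy and can be traced to the prescription: 0.95 × 36.25 = 34.4 Gy. Arm 1 offers no such cross-check.

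**4. Size as a biologically equivalent dose.** With d the dose per fraction and D the total, the equivalent dose in 2-Gy fractions is EQD2 = D × (1 + d/(α/β)) / (1 + 2/(α/β)).

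| Reading | α/β = 1.5 | α/β = 3 |
|---|---|---|
| 38 × 2 Gy = 76 Gy | 76.0 | 76.0 |
| 39 × 2 Gy = 78 Gy | 78.0 (+2.6%) | 78.0 (+2.6%) |
| 38 × 2.053 Gy = 78 Gy | 79.2 (+4.2%) | 78.8 (+3.7%) |

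The ratio 1.5 is the value the Introduction mentions for prostate cancer. The ratio 3 is an assumption, used to show the range.

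**5. Sample size.** The calculation in section 8.0 uses only the acceptable and unacceptable event rates, the significance level and the power. Dose does not enter, so the stated 30 eligible patients per arm does not depend on this point.

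**The case against.** The contradiction itself is hard to dispute. The arguments on the other side are about its reach.

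- **Only one figure is in conflict.** Fraction number and fraction size agree in both places, and PTV2 dose, margins and technique are given. This stands: the ambiguity is the PTV1 total and the limits derived from it, not the whole IMRT arm.
- **The formal SBRT test does not use the control arm.** Each arm is tested against a fixed rate, so the SBRT verdict does not depend on the IMRT dose. This also stands. It leaves exposed the IMRT arm's own verdict and the between-arm comparison named in the primary objective and primary endpoint.
- **Organ limits in absolute Gy give some protection.** The rectum and bladder limits apply whichever total is used, and they restrict the effect on bowel and urinary outcomes. They do not remove it, because the same limits would then govern two different prescriptions.
- **No harm is demonstrated.** Nothing in the protocol shows that patients were treated to different totals, and the effect on EPIC event rates cannot be calculated from it. The protocol names recruiting departments and lists no centres, so the realistic risk is divergence between planners. If all control patients received the same total, there would be no mixture, only a control dose that the protocol misstates in one place. All of this is correct. It limits the claim about the primary analysis but does not excuse an inconsistent prescription.
- **The ratio of 1.5 relates to tumour.** It does not describe bowel or bladder, so the 4.2% figure should not be read as a normal-tissue effect.

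**Conclusion.** The concern holds. The Arm 1 prescription in section 5.0 E is wrong as written, because its three figures cannot all be true, and it disagrees with the Design table. The physical discrepancy is 2 Gy, or 2.6% of 76 Gy. In EQD2 it is 2.6% if 78 Gy means 39 fractions of 2 Gy, and 3.7% to 4.2% if it means 38 fractions, for alpha/beta of 3 (assumed) and 1.5 respectively. The percentage-based Arm 1 planning limits shift by about 1.9 to 2.2 Gy. The finding rests on exact arithmetic and two passages of current text; only the EQD2 range needs an assumption. The document does not show which total is intended. It must be corrected because it sits in a prescribing section and leaves the control dose open, not because damage to the primary analysis has been shown.

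**What to change.** Reconcile the Design table and section 5.0 E so that fraction number, fraction size and total dose for Arm 1 PTV1 agree wherever they appear. The choice of figure belongs to the radiation oncology lead and is not a statistical matter. State in section 5.0 F, in Gy, which dose the Arm 1 percentages refer to, and confirm that the table was written for the reconciled prescription. If patients have already been treated in Arm 1, record delivered fractions, dose per fraction and total for each, and tabulate them in the report so that any mixture is visible.

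The cost is a one-line protocol correction, a clarification in the constraint table and a notice to planners. Sample size, endpoints and tests do not change.

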#### F. Dose constraint/specification

##### Arm 1

| PTV                          | Dmin ≥ 95% of prescribed dose
≤3% received >107% of prescribed dose
≤3% received <93% of prescribed dose |
|------------------------------|----------------------------------------------------------------------------------------------------------------|
| rectum                       | V75Gy ≤ 15%
V70Gy ≤ 20%
V65Gy ≤ 25%
V60Gy ≤ 35%
V50Gy ≤ 50%                                        |
| bladder                      | V80Gy ≤ 15%
V75Gy ≤ 25%
V70Gy ≤ 35%
V65Gy ≤ 50%                                                       |
| femoral head                 | V50Gy ≤ 50%                                                                                                    |
| penile bulb
(recommended) | D70 ≤ 70Gy
D90 ≤ 50Gy                                                                                       |
| normal tissue                | Dmax ≤ 110% of prescribed dose                                                                                 |

##### Arm 2

| Organ           | Volume                              | Dosimetry parameters |
|-----------------|-------------------------------------|----------------------|
| Prostate (PTV1) | Maximum point dose (1 cc)           | ≤38.78Gy             |
|                 | Minimum dose received by 95% of PTV | ≥ 36.25 Gy           |
|                 | Minimum dose received by PTV        | ≥ 34.4 Gy            |
| Prostate (PTV2) | Maximum point dose (1 cc)           | ≤38.78Gy             |
|                 | Minimum dose received by 95% of PTV | ≥ 32.5Gy             |
|                 | Minimum dose received by PTV        | ≥ 30.9Gy             |
| Rectum          | Maximum point dose (1 cc)           | ≤ 38.06 Gy           |
|                 | Less than 3 cc                      | < 34.4 Gy            |
|                 | 90% rectum                          | ≤ 32.625 Gy          |
|                 | 80% rectum                          | ≤29 Gy               |

|                                     |                                         |                                        |
|-------------------------------------|-----------------------------------------|----------------------------------------|
|                                     | 50% rectum                              | $\leq 18.125$ Gy                       |
| Bladder                             | Maximum point dose (1cc)                | $\leq 38.06$ Gy                        |
|                                     | 90% Bladder                             | $\leq 32.625$ Gy                       |
|                                     | 50% Bladder                             | $\leq 18.125$ Gy                       |
| Penile bulb (recommended)           | Maximum point dose                      | No more than 100% of prescription dose |
|                                     | Less than 3 cc                          | 20 Gy                                  |
| Femoral heads
Skin (recommended) | Less than 10 cc cumulative (both sides) | 20 Gy                                  |
|                                     | Maximum point dose                      | 30 Gy                                  |

